### Informed consent, confidentiality, and data management

2.3

All participants will provide consent to participate in the relevant studies. A Participant Information and Consent Form (PICF) relevant to each study will be provided to potential participants prior to taking part in the research studies to which they are invited. Depending on the study, the PICF may be provided in person or via email/post. Written informed consent/assent will be obtained on the day for the healthy lifestyle program and in-person workshops, focus groups, and interviews. For online workshops/focus groups/interviews, informed consent/assent will be obtained prior to the session via online forms. Informed consent will be obtained from the participant if age-appropriate or, when the participants are children, from a caregiver. It will be optional for children and young people to sign the consent form (if age-appropriate). For participants taking part in the online qualitative proformas and evaluation survey, the PICF will be at the start for participants to read and select a box that they consent to participate. All potential participants will be able to ask questions at the time of recruitment and/or contact the research team prior to the study with any queries. There will also be an opportunity for further clarification for those participating in the program, workshops, focus groups, and interviews on the day. All participants can withdraw from the studies at any time. Data will be removed at the time of withdrawal if the withdrawal is prior to participating in the workshop/focus groups and analysis.

All qualitative data will be anonymised, and data from the healthy lifestyle program will be de-identified prior to analysis. Study documents will be stored electronically using password-protected files that only investigators and researchers associated with this project have access to. Consent forms and participant data will be stored separately. Records will be stored for a period of 7 years after completion of the research or until the youngest participant turns 25 years of age (52). Once decided that the data are no longer required, they will be destroyed. Confidential and identifying information about participants will not be included in any publications or reports emanating from the project.

### Study 1: develop the adapted healthy lifestyle program with key partners and Aboriginal and Torres Strait Islander advisors for scale-out

2.4

To identify critical elements and outcomes that will determine program success, especially in relation to place-based and cultural considerations, the following studies will be undertaken.

#### Identify critical elements and outcomes to determine program success

2.4.1

##### Overview

2.4.1.1

Before program commencement, important elements and program outcomes will be identified to provide clear measures of program success with key partners.

##### Aim

2.4.1.2

Identify critical elements and outcomes to determine program success.

##### Study design

2.4.1.3

A qualitative research design including a 3 h workshop and qualitative proformas [open-ended (free-text) surveys] (53–55) during the pre-implementation phase.

##### Participants

2.4.1.4

The workshop will include approximately 30 participants and approximately 80 participants will be invited to take part in the qualitative proformas. For the purposes of this study, key partners for the workshop are defined as participants in health organisation leadership roles and healthcare professionals. The qualitative proformas will incorporate a wider group of participants covering our main definition of key partners outlined earlier.

##### Recruitment

2.4.1.5

Participants will be purposively recruited through Child and Adolescent Community Health, and other key groups, alongside potential referrers. Key partners will be invited to participate in the workshop and online qualitative proforma via email. The online qualitative proforma invites will not include the workshop participants. Background information will be provided regarding the workshop for the online proforma. Weekly follow-up reminder emails to complete the proforma will be made for 4 weeks until it closes. Study data for the proforma will be collected and managed using the Research Electronic Data Capture (REDCap, Vanderbilt, National Institutes of Health) tools hosted at WA Department of Health (61, 62). REDCap is a secure, web-based software platform designed to support data capture for research studies, providing (1) an intuitive interface for validated data capture, (2) audit trails for tracking data manipulation and export procedures, (3) automated export procedures for seamless data downloads to common statistical packages, and (4) procedures for data integration and interoperability with external sources (63).

##### Workshop format

2.4.1.6

Members of our implementation science team will facilitate the workshop (pre-implementation). The workshop will aim to understand program outcomes and how the outcome measures of success would be weighted by importance. The workshop will be supported by digital audience interaction (Slido, Webex by Cisco, London, 2024) to promote active participation and will allow confidential answers to be made. Slido is an audience engagement tool used in real-time meetings, used for ranking, word clouds, and open text (64). The workshop will be audio-recorded.

After introductions and an outline of aims, the workshop will include a presentation about the program and include potential program sustainment and scalability. The organisational Readiness Thinking Tool on implementing the program will be administered to participants (60). Following this, the group will be split into smaller groups to identify critical program success factors and outcome measures to feed back to the group. The original group will re-form to review each group's rankings to reach a consensus on these measures.

##### Qualitative proforma format

2.4.1.7

Qualitative proformas enable individuals to provide detailed information (53–55) and are an established rapid approach (65). The measures of success from the workshop will be provided to the wider key partner group.

##### Analysis

2.4.1.8

Identified outcomes for program success will be categorised as participant, service, and program implementation outcomes (66). These measurements will inform the feasibility of the program alongside more in-depth economic measures. Multi-modal data (e.g., recordings, butchers’ paper, proformas, Slido) will be analysed based on Smith et al. (53) barrier and enabler approach to identify implementation concern that combines Framework Analysis (56) and the Consolidated Framework of Implementation Research (CFIR) (57). This is a flexible approach to qualitative data analysis and has been adapted to suit different contexts, as evidenced by Smith et al. (54). Framework analysis is suitable as it was developed to address specific questions and has an applied research approach that can inform both policy and practice (56). The CFIR is a recognised framework for assessing challenges and drivers in the process of implementing interventions and can be applied to any stage of the evaluation process (54). The analytical process will follow five stages: familiarisation, identifying a thematic framework [the CFIR will be used to identify barriers/enablers of implementation concern (53–55)], indexing, charting, and mapping and interpretation. NVivo 14 will be used to manage the data (67). Permission has been provided by Lumivero to use/mention NVivo as a software tool with all the related studies (67).

#### Identify cultural and place-based considerations for program success

2.4.2

##### Overview

2.4.2.1

When considering scale-out of an evidence-based program, it is important that cultural and place-based considerations are taken into account in any adaptation (68).

##### Aim

2.4.2.2

Identify cultural and place-based considerations for program success.

##### Study design

2.4.2.3

A qualitative workshop.

##### Participants

2.4.2.4

Inclusion criteria: Aboriginal and Torres Strait Islander advisors (*n* ∼ 30) interested in the cultural safety of the program.

##### Recruitment

2.4.2.5

Participants will be purposively recruited through the program's collaborations. Snowball sampling will be welcomed from initial contacts, ensuring diverse participant perspectives.

##### Workshop format

2.4.2.6

An Aboriginal engagement facilitator will conduct the 3-h workshop with support from research team members (pre-implementation). The workshop will commence with an introduction and setting of participation “guidelines” and then review barriers and mitigation strategies for cultural aspects. The format will be a mixture of participants responding as a whole group and working in smaller groups. The workshop will be audio-recorded if consent is obtained, with Butcher's paper for groupwork note-taking.

##### Workshop schedule

2.4.2.7

Areas to be covered: expectations of the program; considerations for developing a healthy lifestyle program for the Perth metropolitan context and how the model can best meet the needs of the community; potential barriers and enablers to engaging with the program; critical elements of the program that will ensure cultural safety and appropriateness; and specific questions around mitigation strategies, group sessions, and planning. Participants will be reimbursed in line with consumer payment guidelines (69) and cost of transport.

##### Analysis

2.4.2.8

The workshop will be analysed using a barrier and enabler approach, combining Framework Analysis and the CFIR (53–55) (see Section 2.4.1.8 Analysis).

### Study 2: assess acceptability, appropriateness, feasibility, and local clinical outcomes of adapted healthy lifestyle program pilot

2.5

To determine the acceptability, appropriateness, and feasibility of the healthy lifestyle program, the following studies will be undertaken.

#### Evaluate the healthy lifestyle program based on participant outcome measures

2.5.1

##### Overview

2.5.1.1

The multidisciplinary healthy lifestyle program will be conducted as a 12-month pilot and includes home-based weight-related assessments and weekly group activity sessions.

##### Aim

2.5.1.2

Evaluate the healthy lifestyle program based on participant outcome measures.

##### Study design

2.5.1.3

The previously outlined studies will inform program design. This research builds on a decade of efficacy studies including an RCT to determine efficacy within the NZ-based program (28, 29). This program scale-out will be evaluated by a single-arm study, with outcomes determined by within-subject change over time.

##### Participants

2.5.1.4

Inclusion criteria: Children and young people aged 4–16 years residing in the East Metropolitan Health Service catchment area referred to the program, with a BMI ≥95th percentile (obesity cut-point), or those with ≥85th percentile (overweight cut-point) with weight-related comorbidities. These cut-points are used in Child and Adolescent Community Child Health, based on Centers for Disease Control (CDC) and Prevention (70) and the American Academy of Pediatrics recommendations (13). Exclusion criteria include significant medical or psychological conditions leading to inability to engage with the program; children/young people without a committed family member, or those with significant weight-related health conditions requiring tertiary input.

A total sample size of 245 is required to accommodate for an estimated 30% drop-out rate as seen in the NZ study (required *n* = 171) over 22 months (29). This sample size can show statistical significance for a mean change in BMI standard deviation score (SDS) of 0.1, with a standard deviation of 0.4 (small effect size), power of 90%, and an alpha of 0.05. A meta-analysis of childhood obesity interventions showed that a change of −0.1 BMI SDS can lead to improvements in cardiovascular and metabolic outcomes (71). Sample size was determined using a two-tailed *t*-test with a difference between two dependent means using change from baseline to 12 months.

##### Recruitment

2.5.1.5

Referrals will come from health professionals within the identified communities, including child and school health nurses, Aboriginal and Torres Strait Islander community-controlled health services, and other professionals involved in the child or young person's care. It is anticipated that some referrals will come from the School Entry Health Assessment at ages 4–5 years old, where growth screening is undertaken. This will provide opportunities to intervene early, which is important given that long-term outcomes are more favourable in younger children (<10 years) (22). Self-referrals will also be received. Promotion of the program will be through Child and Adolescent Community Health, key relevant partners, and primary care organisations and schools. Pathway components are shown in Figure 1.

**Figure 1 F1:**
[figure not shown]
The healthy lifestyle program pathway.

##### Program format

2.5.1.6

The program will undertake weight-related assessments including selected outcome measures at baseline, 6 and 12 months (implementation). Weekly group sessions for participants will be delivered for 6 months. All children referred will be seen in the family home or community location by the Healthy Lifestyle Coordinator (a health professional trained in focused weight-related assessment, supported by a paediatrician). Removal of a hospital-based appointment with a specialist will enable access to the service for larger numbers and priority groups and “demedicalise” the process. An Aboriginal health practitioner (employed by the program) will support families where indicated and needed. The team comprises dietitians, an exercise physiologist, and a psychologist, with paediatrician oversight. Cultural safety of the program will be ensured with Aboriginal and Torres Strait Islander guidance and leadership throughout the project. Table 4 outlines the support provided, with a similar format to the NZ program (28).

**Table 4 T4:** Support to be provided for participants during the healthy lifestyle program.

Support to be provided during the program
Baseline, 6- and 12-month assessments with healthy lifestyle change advice in the home or a community centre (blood tests only when indicated)
Questionnaire review (team), multidisciplinary team meeting following each assessment—review and action of alerts
Community visit/telehealth/phone contact within first month from exercise physiologist and/or dietitian if indicated and accepted, ±Aboriginal and Torres Strait Islander health practitioner (±ongoing support)
Exercise physiologist/dietitian review of progress at 6 months (seen at group if attending)
±Keyworker engagement depending on progress at 6 months
Weekly activity and education sessions for 6 months (total of 26 h contact time)
Total home/community visits offered over 1 year = 3 minimum

##### Assessment format

2.5.1.7

The children and young people will be offered a healthy lifestyle check by a healthy lifestyle coordinator at baseline and 6-monthly for 12 months. Table 5 outlines the key physical assessment measures. Of note, weight status will not be an emphasis with participants.

**Table 5 T5:** Key elements of the physical assessment measures during the program evaluation.

Key assessments	Baseline	6 months	12 months
Resting heart rate	✓	✓	✓
Blood pressure (using Welch Allyn portable sphygmomanometer with flexiport reusable BP cuffs of appropriate size)	✓	✓	✓
Height (to 0.1 cm using average of three readings on Seca 213 portable stadiometer)	✓	✓	✓
Weight (to 0.1 kg using Seca 813 digital scales)	✓	✓	✓
Acanthosis nigricans screen	✓	✓	✓
Ear, nose, and throat examination (using Welch Allyn portable otoscope)	✓	✓	✓
Self-report of Tanner pubertal stage (or from parent in very young children)	✓	✓	✓
Accompanying adult's height and weight	✓		✓
Blood sampling^a^ [only where indicated, may include liver function tests, glycated haemoglobin (HbA1c), and lipid studies]	±	±	±

^a^
Blood sampling will be undertaken only as part of best-practice clinical care (see NZ program methodology paper) (28).

Information will be gathered regarding ethnicity, past medical history, medical conditions, and family history. Questionnaires that will be administered (at baseline, 6, and 12 months) are outlined in Table 6.

**Table 6 T6:** Standardised questionnaires in the healthy lifestyle program evaluation.

Questionnaire	Description
Paediatric Quality of Life Inventory (PedsQL)™ (77–81)	Designed to evaluate health-related quality of life in children/adolescents—has been extensively validated. Self-report and/or caregiver proxy report, depending on age of child or young person (Supplementary Table S1)
Strengths and Difficulties Questionnaire (SDQ) (82)	Behavioural screening questionnaire. Self-report and/or caregiver proxy report, depending on the age of the child or young person (Supplementary Table S1)
CHU-9D (83, 84) and CHU-9D proxy (85) and under 5's (86)	Instrument and proxy version (for caregivers to complete for younger children) utilised to obtain quality-adjusted life years directly for use in cost-utility analysis. (Supplementary Table S1)
Physical activity questionnaire	Questionnaire developed using format similar to aspects of Children's Physical Activity Questionnaire (87)
Physical activity and nutrition knowledge	Open-ended qualitative survey questions [adapted from the NZ Nutrition survey (88)]
Health-seeking behaviour	Closed questions regarding presentations to primary care and hospital in the past 6 months for child/young person similar to resources utilisation questions (89)
Sleep-Related Breathing Disorder Scale from Pediatric Sleep Questionnaire (PSQ-SRBD) (90)	Validated sleep questionnaire for sleep-disordered breathing
Multi-pass 24 h food recall (91)	Dietary questionnaire assessing food and beverage intake in the preceding 24 h
Two-item food insecurity scale (92)	Brief screening tool for food insecurity
ScreenQ (93)	To determine the quantity and quality of screen time

REDCap will be utilised for data collection. Data will be reviewed monthly for validity and completeness. The questionnaire will include alerts for data outside acceptable medical parameters (e.g., elevated blood pressure percentiles) for discussion at multidisciplinary team meetings to individualise patient recommendations. Progress will be captured on a multidisciplinary team worksheet and results of each assessment will be reviewed and further referrals made, as required.

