##### Outcomes

2.5.1.10

Primary outcome measures are change in BMI SDS at 6 and 12 months post-enrolment and change in BMI percentage of the 95th percentile (94). Secondary outcomes include changes in health-related quality of life, dietary intake, physical activity, screen use, knowledge of the benefits of physical activity and healthy eating, and blood pressure and resting heart rate at 6 and 12 months. The Child Health Utility 9D (CHU-9D) instrument (83) will obtain quality-adjusted life years for use in cost-utility analysis (95), and additional economic outcome measures will be examined (e.g., health-seeking behaviour and cost of intervention per person). In accordance with the WA Aboriginal Health and Wellbeing Framework, when ensuring equitable services, two key outcomes are (timely) access to services and cultural appropriateness (41). These will be measured through uptake of participants identifying as Aboriginal and Torres Strait Islander and diverse ethnicities and through focus groups with participants (see Section 2.5.2).

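### For children referred at a recent primary-care or hospital visit, the 6-month look-back can count that visit at baseline only, so part of any observed fall in health-seeking behaviour may be an artefact of entry

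*Protocol article*

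**What the plan says.** Section 2.5.1.7 (Assessment format), Table 6, describes the health-seeking item as "Closed questions regarding presentations to primary care and hospital in the past 6 months for child/young person". On timing, the same section says: "Questionnaires that will be administered (at baseline, 6, and 12 months) are outlined in Table 6". The item therefore looks back over the 6 months before entry, then over months 0–6, then over months 6–12.

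Section 2.5.1.3 (Study design) fixes the comparison: "This program scale-out will be evaluated by a single-arm study, with outcomes determined by within-subject change over time".

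Section 2.5.1.10 (Outcomes) gives the measure its role: "additional economic outcome measures will be examined (e.g., health-seeking behaviour and cost of intervention per person". It is neither a primary outcome nor in the list of secondary outcomes, and no specific test of its change is named.

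Section 2.5.1.5 (Recruitment) describes entry: "Referrals will come from health professionals within the identified communities, including child and school health nurses". Community-controlled health services and other professionals caring for the child are also named. So is school screening: "It is anticipated that some referrals will come from the School Entry Health Assessment at ages 4–5 years old". Self-referral is accepted as well.

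Section 2.5.1.9 (Analysis) adjusts models for age, gender, socioeconomic status and ethnicity, but not for referral source. Nothing in the article flags or sets aside the visit at which the child was referred.

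**The concern.** The baseline window and the follow-up windows are not alike for every child. If a child was referred at a general practice or hospital visit shortly before baseline, having made that visit is part of how the child came to be in the study. The baseline count is then conditioned on a visit, while the 6- and 12-month counts are not. A within-child comparison reads this difference as change, and a single-arm design has nothing to subtract it.

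What is at stake is the economic reading. A fall in presentations could be taken as the program reducing service use. Under section 2.5.3.6 the program outcomes are presented at the end-of-program workshop and the scalability tool is applied to them. Table 1 foresees a business case. If the referring visit is not recorded when the baseline questionnaire is completed, a later analysis may be unable to identify it reliably.

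**Working it through.** **The plan's own figure.** The article states no figure for health-seeking behaviour. Its only sample-size figure is for BMI SDS (section 2.5.1.4): mean change 0.1, SD 0.4, two-sided alpha 0.05, power 90%, paired t-test. The noncentral t calculation gives n = 171 (power 0.902), and 171 / (1 − 0.30) = 244.3, rounded up to 245. Both figures reproduce. I use n = 171 below as the number with follow-up.

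**Inputs that the article does not give (assumed, shown as ranges).**
- L: usual presentations per 6 months, the same in every window: 1, 2 or 3.
- p: share of children whose referral was made at a counted presentation within 6 months before baseline: 0.25, 0.5 or 0.75. This definition already absorbs the unknown interval from referral to baseline.
- The answer is taken to be a number. Table 6 says only that the questions are closed.
- Visits occur at random (Poisson), so the referring visit comes on top of the usual L.
- No program effect.

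**Expected counts.** Baseline mean = L + p. Follow-up mean = L. Expected change = −p. Apparent fall = p / (L + p).

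| L | p = 0.25 | p = 0.5 | p = 0.75 |
|---|---|---|---|
| 1 | 0.25/1.25 = 20% | 0.5/1.5 = 33% | 0.75/1.75 = 43% |
| 2 | 0.25/2.25 = 11% | 0.5/2.5 = 20% | 0.75/2.75 = 27% |
| 3 | 0.25/3.25 = 8% | 0.5/3.5 = 14% | 0.75/3.75 = 20% |

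At p = 0 the apparent fall is zero. A self-referred or school-screened child with a usual rate of 2 has expected counts 2, 2, 2. A child referred at an additional clinic visit has 3, 2, 2.

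**Scale against sampling error.** The SD of the paired change is √(2L + p(1 − p)). The chance of a significant fall is about Φ(p√171 / SD − 1.96). For L = 2 and p = 0.5: SD = √4.25 = 2.06, 0.5 × 13.08 / 2.06 = 3.17, and Φ(3.17 − 1.96) = 0.89. A simulation that also let visit rates vary between children gave 88% here, 36% at p = 0.25 and over 99% at p = 0.75, against a nominal 2.5%. These figures show that the artefact could be large relative to noise. They are not the error rate of a planned test, because none is named.

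**When the visit is not additional.** Suppose a fraction r of the referring visits are additional and the rest are scheduled visits that would have happened anyway. With no program effect:
- visit included: expected change = −p·r
- visit excluded: expected change = +p·(1 − r)

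At p = 0.5 and r = 1 these are −0.5 and 0. At r = 0.5 they are −0.25 and +0.25. At r = 0 they are 0 and +0.5. The two versions always lie on either side of, or at, the true value of zero. That is the reason to report both.

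**The case against.** The strongest case against is that much of this rests on facts not in the article.

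- **Share and interval.** Neither p nor the referral-to-baseline interval is stated. Child and school health nurses are the first referrers named, and it is not said whether such contacts count as primary care. This stands: the size cannot be fixed from the article, only bounded under assumptions.
- **Format.** The closed questions might be banded or yes/no, in which case the arithmetic above does not carry over directly. This also stands, although the asymmetry between windows remains.
- **Regular attenders.** A child with two scheduled visits per 6 months who is referred at one of them records 2, 2, 2. Deleting the visit gives 1, 2, 2, a false rise. This stands, and it rules out deletion as the only analysis.
- **Visits generated by the program.** Assessments are followed by team review and further referrals where needed (Table 4 and section 2.5.1.7), which can add visits after baseline. If q is the mean number of such visits per child, the net change is q − p. At p = 0.5 it is −0.3, 0 and +0.3 for q = 0.2, 0.5 and 0.8. So the direction of the observed change is not settled. These visits are real use caused by the program, however, and belong in its economic result. Where they cancel the entry artefact, the artefact hides them.
- **Condensed article.** Item wording is normally left to the questionnaire or a health-economics plan, neither of which is shown. That lowers the weight of the point. The look-back, the time points and the within-subject comparison are nevertheless stated here.

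A reader might infer that this measure will show a fall even if the program does nothing. The article does not support that, for the reasons above.

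**Conclusion.** The point holds in a limited form. For children referred at a primary-care or hospital visit within 6 months before baseline, the question as described can count that visit at baseline only, and the single-arm design cannot remove the resulting asymmetry. Part of any observed fall may therefore be an artefact of entry.

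Under random visits at 2 per 6 months with every referring visit additional, the apparent fall is 11% to 27% for p from 0.25 to 0.75. Over usual rates of 1 to 3 it ranges from 8% to 43%. It shrinks towards zero as p falls or as more referring visits are ones that would have happened anyway. Usual rate, share and visit pattern are all assumptions.

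The primary outcomes, the listed secondary outcomes and the sample size are untouched. This is a cheap improvement to an additional economic outcome, not an error in the main analysis.

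**What to change.** 1. At baseline, record whether one of the reported presentations was the one at which the child was referred to this program. One tick-box in the REDCap questionnaire is enough, or referral source and date can be taken from the client referral form already listed in Table 2.
2. Report the change in service use twice, with and without that visit.
3. State in advance that a fall will not be attributed to the program unless it remains when the visit is excluded.
4. If months 6–12 are also compared with months 0–6, label that descriptive. It avoids the baseline count but has no pre-program reference.

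The cost is one tick-box at most and a sentence or two in the analysis text. The downsides are some recall error in identifying the visit, possible over-correction for children with regular scheduled visits (hence both versions), and a possibly less favourable result.
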